### Sample size

There are four clusters—two intervention and two control areas—in the feasibility trial. In each of these areas, we will engage 10 VHTs to recruit participants. Each VHT will aim to recruit 35 women over a 6-month period, so in total, we will aim to recruit about 1400 women. A formal sample size calculation is not required for a feasibility study, but a sample of this size will allow us to estimate the key parameters for a future full-scale trial, including the variability, clustering and retention rate.

For the process evaluation, we will use a “purposive” sampling approach to select respondents (according to socio-demographic and organisational factors expected to influence the delivery or effectiveness of the intervention). We plan six separate FGDs, each of six to ten participants, two each for the following categories of individuals: (a) postpartum women—the age will determine their allocation to subgroups: adolescent girls (≤ 20 years), women 21 years and above; (b) men who are partners or husbands of women who deliver during the study; and (c) VHTs involved in the study. We will conduct about 20–30 in-depth interviews with clinic managers, health service providers, VHTs and couples. We will interview postpartum women and their partners, who took up, and who did not take up, the offer of couples’ counselling at home and at ANC and the offer of a contraceptive method, in order to understand the factors influencing their decisions, their experience of the intervention and their suggestions for improving it. We will also ask about the degree of contamination between study areas and will assess this as a feasibility outcome.

### Statistical analysis plan

The primary analysis will determine whether the study is feasible. Data will be explored descriptively and graphically for all feasibility outcomes including the intervention uptake, adherence, attrition, retention and the number of participants recruited per site. We will estimate the variance of proposed outcome measures; alongside previous literature, this will be helpful in a future sample size calculation. We will also estimate the intra-cluster correlation coefficient (ICC), and its 95% confidence interval, at both the randomisation and VHT level. Whilst these estimates are not by themselves sufficient for a future calculation, they can be compared to the existing literature and give some reasonable bounds for future estimates as well as allowing us to explore at which level clustering may be present so that this may be factored into the future design.

All participant data will be included in the analyses, including those who have withdrawn, unless the participant specifically requests that their data be removed. The pattern and frequency of missing data will be explored descriptively to determine whether there are outcomes or items on instruments that participants opted not to complete. This may inform the decision about measures for a full trial.

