### Assignment of intervention or control

Clusters are at the level of the health centre III (sub-county). In all the villages surrounding a health facility, all the couples will be in the same group. Two urban and two rural health centre IIIs will be randomly selected from a list of all health centre IIIs in Mbarara District (rural) and Mbarara city (urban), in south-western Uganda. We will use a stratified randomisation according to urban/rural location. Participating health facilities will be randomised during a meeting in which the district health officer is invited to draw pieces of paper out of a hat, to determine whether each health centre is assigned to the intervention or control arm—so that the randomisation process is open and understood by all. It will not be possible to blind participants or care providers. If two of the selected sub-counties share a boundary, we will only include women intending to attend ANC and PNC in their area, in order to minimise contamination.

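### With four health centres, one per arm-by-stratum cell, the ICC at the randomisation level is too imprecise to bound the main trial's design effect; the VHT-level ICC is usable

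*Protocol article*

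**What the plan says.** All references are to the protocol article.

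- **Sample size:** "There are four clusters—two intervention and two control areas—in the feasibility trial". Each area has 10 recruiting VHTs, with a target of 35 women per VHT and about 1400 in all. No formal calculation is offered, but "a sample of this size will allow us to estimate the key parameters for a future full-scale trial", and clustering is named as one of those parameters.
- **Assignment of intervention or control:** "Clusters are at the level of the health centre III (sub-county"). "Two urban and two rural health centre IIIs will be randomly selected", and "We will use a stratified randomisation according to urban/rural location".
- **Statistical analysis plan:** the ICC will be estimated "and its 95% confidence interval, at both the randomisation and VHT level". The authors acknowledge that the estimates cannot carry a future calculation alone, then say "they can be compared to the existing literature and give some reasonable bounds for future estimates". They add that the estimates will let them explore at which level clustering occurs, so that the future design can allow for it.

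The article gives no anticipated ICC and does not say whether the ICC model adjusts for arm or stratum.

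**The concern.** How well an ICC is estimated at a given level depends mainly on the number of units at that level. At the randomisation level there are four, and enrolling more women in each cannot make up for that.

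The four are also fully used by the design. Two urban and two rural centres, randomised within stratum to two arms, give exactly one centre per cell. Any difference between centres is therefore mixed with arm and location. Removing arm and stratum leaves almost no information on between-centre variance. Leaving them in means the ICC counts any intervention effect and any urban/rural difference as clustering.

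The Discussion names a fully powered cluster-randomised trial as the next step, and the randomisation-level ICC is a main driver of its size. Two mistakes are possible: treating a nearly empty interval as a planning bound, or reading a chance estimate of zero as evidence that health centres do not cluster.

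**Working it through.** **Inputs from the protocol.** 4 health centres, 10 VHTs each, 35 women per VHT.

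**The plan's own figure.** 4 × 10 × 35 = 1400, or 350 per centre and 700 per arm. It reproduces.

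**Assumptions.** The observed ICC values of 0.02 and 0.05 are mine, since the protocol gives none. Clusters are of equal size, and normal theory is used as an approximation for binary outcomes.

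**Step 1: health-centre df.** Four centre means, less the rank of the fixed part of the model:

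| Fixed terms | Residual df |
|---|---|
| none beyond the mean | 4 − 1 = 3 |
| arm | 4 − 2 = 2 |
| arm + stratum | 4 − 3 = 1 |
| arm + stratum + interaction | 4 − 4 = 0 |

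**Step 2: exact one-way F interval.** With m women per cluster, F = (1 + (m − 1)ρ)/(1 − ρ). Each limit is (F/c − 1)/(F/c + m − 1), where c is the 97.5% point of the F distribution for the lower limit and the 2.5% point for the upper.

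Health-centre level: m = 350, denominator df = 1400 − 4 = 1396.

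- ρ = 0.02: F = (1 + 349 × 0.02)/0.98 = 7.98/0.98 = 8.14
- ρ = 0.05: F = (1 + 349 × 0.05)/0.95 = 18.45/0.95 = 19.42

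Worked case, ρ = 0.05 with 2 df: c = 3.699 and 0.0253.

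- Lower: 19.42/3.699 = 5.25, so 4.25/354.25 = 0.012
- Upper: 19.42/0.0253 ≈ 767, so 766/1116 = 0.69

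| Observed ICC | 3 df (arm and stratum left in) | 2 df (arm out) | 1 df (arm + stratum out) |
|---|---|---|---|
| 0.02 | 0.005 to 0.243 | 0.003 to 0.478 | 0.002 to 0.960 |
| 0.05 | 0.015 to 0.435 | 0.012 to 0.686 | 0.008 to 0.983 |

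Testing the health-centre mean square against the VHT mean square (36 df), with a VHT-level ICC of 0.02 to 0.05, widens these slightly. For an observed 0.02 with 1 df the interval becomes 0.000 to 0.96 or 0.97.

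**Step 3: design effect.** 1 + 349ρ, if the main trial also had 350 women per cluster (an assumption; its cluster size is not stated).

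- Observed 0.02: about 2.2 to 168 (2 df), 1.6 to 336 (1 df)
- Observed 0.05: about 5 to 241 (2 df), 4 to 344 (1 df)

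**Step 4: chance of a zero or negative estimate.** This is the probability that an F variate on (df, 1396) falls below (1 − ρ)/(1 + 349ρ), with ρ now the true ICC.

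- True 0.02: 27% (1 df), 12% (2 df)
- True 0.05: 18% (1 df), 5% (2 df)

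**Step 5: what 3 df would absorb.** Suppose uptake is 20% in one arm and 30% in the other, with no clustering at all (illustrative). The between-centre component is 4 × 0.05²/3 = 0.0033. The average within-centre variance is (0.16 + 0.21)/2 = 0.185. The apparent ICC is 0.0033/(0.0033 + 0.185) ≈ 0.018, all of it intervention effect.

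**Step 6: VHT level.** Health centre fixed, m = 35, df = 40 − 4 = 36 and 1400 − 40 = 1360.

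- Observed 0.02: F = 1.68/0.98 = 1.71, CI 0.004 to 0.052
- Observed 0.05: F = 2.70/0.95 = 2.84, CI 0.024 to 0.098

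**The case against.** The strongest reply is that the authors have already hedged. They say the estimates are not enough alone and will be set beside the literature, they report a confidence interval that will show the imprecision, and they state no precision target. The bounding sentence covers both levels, and at VHT level it is true. The statement in Sample size names no level. The covariates of the ICC model are the kind of detail an article leaves to the full analysis plan.

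Much of this stands. A reader might infer that the health-centre ICC cannot be estimated at all, or that no bounds exist. The documents do not support that. Estimability is lost only if the arm-by-stratum interaction is fitted, which the plan does not specify; otherwise an estimate and an interval can be computed. A reader might also infer that the planners will size the next trial from this ICC alone, and the plan disclaims that.

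The caveat does not rescue the health-centre half of the claim. An interval such as 0.003 to 0.48 adds almost nothing to a literature range, so any useful bound would come from the literature. Nor does the caveat cover the aim of seeing where clustering lies, since the estimate can be zero by chance under real clustering. Leaving the model open does not help either: none of the four choices in Step 1 gives a narrow interval free of arm and location.

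**Conclusion.** The point holds for the randomisation level only. Once arm, or arm and stratum, is allowed for, the health-centre ICC rests on 2 df or 1 df. For observed ICCs of 0.02 to 0.05, its 95% interval has an upper limit between 0.48 and 0.98. That does not usefully bound the main trial's design effect and cannot show that health-centre clustering is absent. Keeping all 3 df narrows the interval to 0.005–0.243 (observed 0.02) or 0.015–0.435 (observed 0.05), but changes what is estimated. The VHT-level claim is sound.

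The exact limits depend on the assumed ICCs, equal cluster sizes and normal theory. The conclusion follows from the df.

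Severity is moderate and not a must-fix. The primary analysis concerns feasibility, and none of its outcomes uses the ICC.

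**What to change.** In Sample size and Statistical analysis plan:

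1. Limit the statements about estimating clustering and bounding future values to the VHT level.
2. Specify that the VHT-level ICC is estimated with health centre as a fixed effect, which also removes arm and stratum.
3. State that the health-centre ICC rests on only 1 to 2 df after allowing for arm and stratum, is too imprecise to bound the main trial's design effect or to show that clustering at that level is absent, and is reported descriptively only.
4. State that the planning range for the health-centre ICC will come from external multi-cluster data and be carried through the main-trial calculation as a range.

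The cost is a few sentences and one model specification, with no change to recruitment, randomisation or data collection. The downside is that the feasibility trial's stated yield becomes less favourable.

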### Qualitative analysis plan

In-depth interviews and focus group discussions will be transcribed verbatim and translated into English, where English was not the language used during the interview, into Microsoft Word documents and analysed in Atlas.ti®. Thematic content analysis will be used [39]. Individual interviews or focus group discussions will constitute the units of analysis. At least two investigators will code the first three interviews/focus groups and will independently propose a coding framework. The coding framework will be discussed with the wider team before being finalised and applied to the interviews.

### Cost effectiveness

Quantitative data on the role of costs both formal and informal in relation to the intervention will help in the design of a cost-effectiveness study. The cost-effectiveness of the intervention versus control depends on the additional cost of the intervention plus any knock-on effects on other costs. In this feasibility stage, both of these will be explored. We will evaluate the different ways of delivering the intervention in relation to its cost, given that the method of delivery may have to vary by place. The standard questionnaires will include questions about the costs of different components of care in both groups. The aim will be to assess in the process evaluation the likely cost of the intervention if delivered in different ways and to guide how it might be delivered most efficiently in the main trial. The knock-on effects of such an intervention, which may be diffuse (such as travel to the venue, time off work and cost of measures to encourage spouse attendance) will also be explored qualitatively in the process evaluation. We will also explore in an open-ended way what other non-healthcare costs might be incurred by trial participants. One perspective often adopted for costing is that of the health care provider, and this will be a perspective included in the main trial.

Cost per birth averted is likely to be the measure of cost-effectiveness in the main trial but the appropriateness of this will also be explored particularly with the local health service leaders and taking account of other relevant work in the field and in terms of policy alternatives. Cost per quality-adjusted life year (QALY) is not usually seen as appropriate for interventions to do with fertility control. Thus, consideration will be given to the inclusion of other secondary outcomes by use of an impact inventory which will list all the effects, both to do with outcomes and resource use, of the intervention. The eventual cost-effectiveness analysis will compare the results from the trial with those in the relevant literature.

### Data management plan

Each participant will be given a unique identification number. Data entered via the COSMOS database is automatically backed up to 3 different data centre regions. All collected data is automatically deleted from mobile devices after successful synchronisation to the COSMOS database. Downloaded data and manually entered data will be stored on password-protected computers. All access to data is very tightly and strictly controlled by the University of Southampton. Transcripts from interviews and focus groups will also be anonymised and shared between the research groups. At the time of publication, we will make the anonymised data freely available on a data repository of the University of Southampton.

### Data security and confidentiality

COSMOS uses built-in advanced encryption technology (AES256) to safeguard data and meet obligatory commitments towards data protection. Data entry directly into the COSMOS system minimises the risk of data loss or breach of confidentiality. The VHTs will use a lockable cupboard to keep documents. The research assistant will monitor this and will collect study documents on a regular basis and transfer the documents to the secure locked cabinet in the study office. The study database will be password-protected and will be stored on a password-protected computer. Data entered into the study database will be anonymised.

Qualitative data will be recorded on a digital voice recorder, which will also be stored securely in a locked cabinet in the research office. The recordings will be transferred to a secure password-protected computer. They will be transcribed and translated into a Word document on the same computer where the recordings are downloaded, omitting any names so that transcripts are also anonymous. Once the transcripts have been checked and corrected, if necessary, the voice recordings will be deleted.

### Ethical and regulatory aspects

Randomised controlled trials have special ethical concerns and the ethical reason for randomly assigning the intervention arm is because we expect both arms to be at a state of equipoise. For the purpose of this feasibility trial, the research participants in the control arm have access to standard care that is deemed adequate healthcare by the Ugandan Ministry of Health.

The study was approved by MUREC (the Mbarara University of Science and Technology Research Ethics Committee, Ref #. 16/06-20) and the University of Southampton, Faculty of Medicine Ethics Committee (Ref #. ERGO 54459.R3). All the study methods and procedures will be conducted in accordance with MUREC’s guidelines and regulations. Written informed consent will be obtained from participants of the study. In the case of illiterate participants, they will be asked to use a thumbprint, and an independent witness will sign to confirm that they gave their consent freely in line with the MUREC guidelines. We will train all research assistants and village health teams in relevant principles of good clinical practice, particularly taking informed consent, and confidentiality. All protocol modifications will be communicated to MUREC for approval before they are implemented, and protocol modifications relevant to health care provision will be communicated to study sites. The currently approved version of the protocol is version 2, dated July 29, 2020. We are required to report any deviations from the protocol to the Mbarara University of Science and Technology Research ethics committee. The study will comply with the data protection guidelines of the University of Southampton.

This trial has an independent Trial Steering Committee (TSC) that acts as the oversight body on behalf of the sponsor and funder. At least half of the members, including the chair, are independent. The committee will meet at least once a year. No Data Monitoring and Ethics Committee will be convened for ACCU, as this role will be assumed by the TSC. The role of the Trial Steering Committee is to ensure the trial is on track as set out in the protocol, to ensure the safety of the patients, to help deal with any problems or issues that might arise and to advise the principal investigators and co-investigators. Among the terms of reference of the steering committee, as stipulated in their charter, is to recommend whether to continue or terminate the study or further adapt it based on safety and efficacy considerations.

## Discussion

With the current COVID situation, it was felt best not to set numerical progression criteria which we may fail to attain due to constraints of the COVID-19 lockdowns. However, we will carefully monitor the rate of recruitment and percentage of participants followed up, in order to determine whether progression is feasible and to learn how these could be improved in a full-scale trial. If this trial demonstrates the feasibility of recruitment and delivery, we will seek funding for a fully powered cluster-randomised trial of the intervention. We will use data from the process evaluation (involving potential clients, village health teams and health workers), as well as feedback from district health teams and the Ministry of Health, to optimise the intervention package as well as trial procedures.

The methodology of asking VHTs to collect research data using smartphones is innovative. VHTs have previously been asked to collect routine health data using mobile phones, but this will be the first time that the COSMOS software is used by VHTs to collect research data, which will be uploaded in real time to a secure database. There are a number of challenges: some VHTs have a very basic level of education and patchy mobile phone networks, and some villages do not have electricity. We will test ways of overcoming these barriers. If this system works, it could be of great benefit to a wide variety of researchers collecting data from community-based interventions in Uganda and elsewhere in Africa, making the data collection quicker, cleaner and more secure than traditional paper-based questionnaires.

In order to assess the effectiveness of our intervention in a cluster-randomised trial, there should be no information sharing (“contamination”) between the experiment and control arms. However, with ease in transport and availability of telecommunication services, people in the intervention clusters may share their health information with the control arm population. This feasibility trial will also enable us to ascertain whether “contamination” occurs between clusters.

Understanding the effectiveness of an antenatal couples’ counselling intervention for improving the appropriate place of delivery and uptake of postpartum contraception in Uganda, in a resource-constrained setting like Uganda, is critical for creating public awareness, influencing policy recommendations and developing effective interventions.

### Dissemination plan

We will hold dissemination meetings with stakeholders at the local and national levels to present our results at the end of the project. We will have community meetings to disseminate the findings. We will write up our scientific research in an academic paper which will be submitted for publication in a peer-reviewed scientific journal. We will also submit abstracts to relevant conferences. We will post a summary of our important results on the project website, hosted by the University of Southampton.

### Status of the study

The recruitment and follow-up of participants started in February 2021 and are still ongoing.

## Data Availability

At the time of publication, we will make the anonymised datasets freely available on a data repository of the University of Southampton, eprints.soton.ac.uk. In accordance with the University of Southampton’s data policy, the data will be archived from a minimum of 10 years after publication or last access, whichever is longer. DOIs will be issued for the dataset and data subsets as per the University’s DOI policy. As this is a feasibility study, the study team will have exclusive use of data until the end of the follow-on trial as sharing may prejudice the subsequent study and related publications. The data can be accessed by other researchers on reasonable request to the corresponding author at the end of the study.

## Abbreviations

ANC: Antenatal clinic
BP/CR: Birth preparedness and complication readiness
FGDs: Focus group discussions
QALY: Quality-adjusted life year
GPS: Global positioning system
HIV: Human immunodeficiency virus
IUD: Intrauterine device
LARC: Long-acting reversible contraceptive
MoH: Ministry of Health, Uganda
MUREC: Mbarara University of Science and Technology Research Ethics Committee
PNC: Postnatal care
PPFP: Postpartum family planning
RCT: Randomised controlled trial
SBA: Skilled birth attendant
TSC: Trial Steering Committee
UBOS: Uganda Bureau of Statistics
VHTs: Village health teams
WHO: World Health Organization
